### Participant recruitment—inclusion criteria/exclusion criteria

#### Inclusion criteria

Women will be eligible to enroll in the trial if they meet the following criteria:

(a) Between the ages of 25 and 75 years; (b) pathological diagnosis of BC; (c) patients undergoing mastectomy including unilateral total breast or breast-conserving surgery, with a positive SLNB result, for whom affected axillary lymph nodes have been removed; (d) postoperative chemotherapy or radiation therapy according to the condition; (e) no other malignant tumors within 5 years; (f) no physical therapy-related contraindications; and (g) willingness to sign the informed consent form.

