### Assessment for training

After providing informed consent, participants will be asked standardized questions about their demographic characteristics and medical history. Clinical data will be extracted from the medical records regarding primary tumor, time of primary diagnosis, surgical operation, physical examination, laboratory testing, and imaging examination. To ensure the safety of the training, a therapist will evaluate the patient’s overall health, including physical function, physical activity, mental status, and PDV. Next, the training intensity will be adjusted before patients begin the training. The assessments will include upper limb mobility, grip, limb circumference, PDV, and pain.

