The six measurements will be tested at postoperative 1 day, 3 days, and 1 week, after which the patients will visit the hospital for evaluation once every other week. The ROM, muscle strength, and grip strength results will be used as criteria for maximum exercise intensity settings, and pain, PDV, and limb circumference will be used as indicators to assess whether exercise intensity is appropriate. Exercise intensity will set based on the current test results. If the evaluation index deteriorates, the intensity should be adjusted appropriately.

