### Data analysis

#### Sample size

By estimating the sample size of the k-group sample mean comparison in a completely random design, the improvement scores for the CMS of the four groups of patients at 84 days after treatment were 15, 16, 18, and 19, and the standard deviations were 2, 2.5, 2.5, and 3, respectively. The assumption was that *α* = 0.05 and 1-*β* = 0.9. After calculation using PASS software (11.0), a total of 164 patients were required to be treated, and a 20% loss rate was calculated. Each group required 50 patients [39].

The calculation formula was as follows:
$$ n=\frac{\psi^2\left[{\sum}_{i=1}^k\frac{S_i^2}{k}\right]}{\left[{\sum}_{i=1}^k\frac{{\left(\overline{X_i}-\overline{X}\right)}^2}{\left(k-1\right)}\right]}. $$

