### Statistical analyses

Analyses will be performed using SPSS statistical software (version 20.0) by a statistician in the Department of Rehabilitation Medicine, Zhongnan Hospital of Wuhan University. Data will be analyzed according to the “intention-to-treat” (ITT) principle. A two-sided significance level of 5% will be used for all analyses. If the experimental data satisfies the normal distribution and the homogeneity of the variance, one-way analysis of variance (ANOVA) will be performed for comparison among the 4 groups with respect to the CMS, EORTC QLQ-BR23, SF-36, ROM, strength, grip, circumference, PDV, and pain. If there is an overall difference, the Tukey method for multiple comparisons will be used to compare the differences between groups at each time point. The results of repeated measurement ANOVA testing at each time point in each group will be analyzed by repeated measures to observe the recovery of patients at different times after surgery. For data with irregular variance, variable transformation can be used after the Kruskal-Wallis *H* test.

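### The CMS comparison is fixed as an unadjusted one-way ANOVA although age, type of surgery and day 1 grip are recorded before the arms diverge: valid, but it gives up precision at almost no cost

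*Protocol article*

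**What the plan says.** Under Statistical analyses the article names the between-group test: "one-way analysis of variance (ANOVA) will be performed for comparison among the 4 groups with respect to the CMS", and the same test for every other outcome. If the overall test is positive, "the Tukey method for multiple comparisons will be used to compare the differences between groups at each time point". On alpha: "A two-sided significance level of 5% will be used for all analyses". No covariate appears. The repeated-measures ANOVA is described within each group, to follow recovery, and the Kruskal-Wallis fallback is also unadjusted.

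The variables that could be used are recorded elsewhere in the article:

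- **Age.** Inclusion criteria admit women of 25 to 75 years. Under Assessment for training, "participants will be asked standardized questions about their demographic characteristics and medical history".
- **Type of surgery.** Inclusion criteria admit "patients undergoing mastectomy including unilateral total breast or breast-conserving surgery", and the operation is extracted from the medical records.
- **Day 1 measurements.** "The six measurements will be tested at postoperative 1 day, 3 days, and 1 week" (Assessment for training). Secondary parameters confirms day 1 for grip.

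Training timelines has all groups start phase 1 on day 1. The first planned difference is on day 3, when groups C and D start phase 2. Secondary parameters first schedules shoulder function, the CMS, at 1 week. Concealed randomization and blinding gives a 1:1:1:1 allocation and names no stratification factor.

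**The concern.** A one-way ANOVA has group as its only term. Any variation in CMS that age, operation or early hand strength could explain stays in the error term and widens every interval. If the groups differ by chance on such a variable, the realised difference between them carries part of that imbalance.

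This matters more here than in a two-arm trial with large effects. The sample size section plans on steps of only 1 to 2 CMS points between neighbouring groups. The stated goal is an optimal timeline, which needs the pairwise contrasts and cannot be read from the overall test. The usual remedy, adjusting for the outcome's own baseline, may not be available, because the first CMS in the schedule comes after C and D have diverged. Covariates of this kind would then be the main pre-divergence information for the primary outcome.

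**Working it through.** **Inputs.** From Sample size: "the improvement scores for the CMS of the four groups of patients at 84 days after treatment were 15, 16, 18, and 19". Read in the order A, B, C, D, the contrasts are A v B = 1, C v D = 1, B v C = 2, A v C = 3, B v D = 3 and A v D = 4 points. The same section assumes SDs of 2, 2.5, 2.5 and 3 in that order. Planned enrolment is 50 per group with 20% loss, so 50 × 0.8 = 40 analysed per group.

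**The plan's own figure.** Mean variance = (4 + 6.25 + 6.25 + 9)/4 = 6.375, so the common SD = 2.52. The squared deviations of the means from 17 sum to 10. The noncentral F distribution at alpha 0.05 and 90% power gives 11 per group (44 in total). The printed formula with ψ = 2.17 gives 2.17² × 6.375/(10/3) ≈ 9.0 per group. The stated 164 (41 per group) is not reproduced; it would need a common SD of about 5.3. That is a separate matter, and this point does not depend on it. With 40 per group, power of the overall test is above 99.9% on the stated inputs, so any gain lies in the pairwise contrasts.

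**Effect of adjustment.** R² is the share of CMS variance explained by the covariates. It is assumed.

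- SE of a pairwise difference = √(2 × 6.375 × (1 − R²)/40).
- Tukey critical t = q(0.95; 4, 156)/√2 = 3.673/√2 = 2.597. With three covariates (153 df) it is unchanged to three decimals.
- Power is from the noncentral t distribution with noncentrality = difference/SE.
- Equivalent unadjusted sample = 160/(1 − R²).

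| R² | SE | 1 point (A v B, C v D) | 2 points (B v C) | 3 points (A v C, B v D) | Equivalent n |
|---|---|---|---|---|---|
| 0 (plan) | 0.565 | 21% | 83% | 99.6% | 160 |
| 0.05 | 0.550 | 22% | 85% | 99.8% | 168 |
| 0.10 | 0.536 | 24% | 87% | >99.8% | 178 |
| 0.20 | 0.505 | 27% | 91% | >99.9% | 200 |
| 0.30 | 0.472 | 32% | 95% | >99.9% | 229 |

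**Which contrasts matter.** Aim of this study asks about active shoulder exercise from day 3 and resistance training from week 3. By Training timelines, the first question is A v C and B v D (3 points each), and the second is A v B and C v D (1 point each). B v C changes both timings in opposite directions and answers neither aim; it is shown only as the 2-point case.

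**Sensitivity to the SD.** At SD 5.3, Tukey power for A v D rises from 78% to 81%, 83%, 88% and 92% at R² 0.05, 0.10, 0.20 and 0.30.

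**Chance imbalance.** Assume 70% have total mastectomy (the documents give no mix) and randomisation is unstratified. By simulation with 40 per group, the mean gap between the highest and lowest group is 15 percentage points, and the chance of a gap of 20 points or more is 26%. In CMS points: if operation type alone explained 10% of the variance, its effect would be √0.10 × 2.525/√(0.7 × 0.3) = 1.74 points. A 15-point gap would then move the difference by 0.15 × 1.74 = 0.26 points, against an unadjusted SE of 0.565.

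**The case against.** The strongest reply is that nothing here is wrong. A one-way ANOVA of randomised groups is valid, and its standard error already allows for chance imbalance. The article condenses a fuller protocol, and covariate lists are often left to the analysis plan. The documents give no evidence that age, operation or grip predicts CMS, and without a baseline CMS a low R² is the more plausible. On the plan's own figures no judgement of adequacy changes for the stated aims: the 3-point contrasts are nearly certain without adjustment, and the 1-point contrasts stay far below 90% with it.

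Most of this stands, and it limits the weight of the point. It does not remove it. The article is not silent on the model: it names a test that has no covariates, so the choice is fixed in the text.

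Three stronger readings are tempting and not supported:

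- **That the unadjusted result is biased.** Over repeated randomisation it is not. Imbalance adds random error to one realised estimate, and the worked example gives about a quarter of a point.
- **That no CMS exists before divergence.** The outcome schedule points that way, but the sample size uses improvement scores, which imply a starting value. The abstract lists day 1 and day 3 assessments for all subjects without tying them to CMS, and the design figure is not shown. Absence is likely, not settled.
- **That allocation is unstratified.** The article names no factor, which in a condensed report is weak evidence. If there are strata, a one-way ANOVA ignores them, which is a further reason to adjust.

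**Conclusion.** The point holds as a matter of efficiency. The protocol fixes an unadjusted comparison for its primary outcome while three usable covariates are recorded before the groups' training first differs. For assumed R² of 0.05 to 0.30, SD 2.52 and 40 per group, Tukey power gains 1 to 11 percentage points for a 1-point contrast and 2 to 12 for a 2-point contrast. It gains essentially nothing for the 3-point contrasts.

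The lower end of that range is the safer expectation. A reader might infer that adjustment rescues the resistance-training comparison; at 22–32% power it does not. The facts about the model and the timing of the measurements are firm. The size of the benefit is not, because R² is assumed and the SD comes from a sample size section whose total does not reproduce. The change is worth making because it is nearly free.

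**What to change.** Under Statistical analyses, replace the one-way ANOVA for CMS at the primary time point (the sample size uses day 84) with a linear model (ANCOVA) containing group, age, type of breast surgery (total v conserving) and day 1 grip, stating which arm's value is used. Fix the list before unblinding. Report Tukey-type contrasts of adjusted means with 95% confidence intervals, and keep the unadjusted ANOVA as a sensitivity analysis.

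State whether a CMS value is taken before day 3. If it is, add it as a covariate. Do not adjust for the week 1 CMS, which follows the start of phase 2 in groups C and D, or for chemotherapy or radiotherapy received, which comes after allocation. Do not use day 3 ROM either. Assessment for training implies a day 1 ROM, but the outcome schedule starts ROM on day 3, the day the groups diverge, so grip is the cleaner choice. Day 1 grip may be taken after allocation, but it precedes any planned difference in training.

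The cost is 3 error degrees of freedom (156 to 153) and a change of wording. No new data are needed.

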A meta-analysis of randomized controlled trials has shown that postoperative physical therapy has beneficial effects on BC sequelae and thus can improve shoulder function, reduce lymphedema risk, and improve the quality of life [12]. Among all kinds of therapy modalities [13–15], active exercises and stretching have been proven to be much more effective in the treatment of upper limb dysfunction than other modalities [16, 17], and accordingly, active exercises and stretching are recommended by clinical guidelines [18]. Active exercises have important physiological benefits in maintaining the blood and lymphatic flow to joints and soft tissues, which can prevent the shortening and weakness of the surrounding muscles and connective tissues that may occur following immobilization after surgery [15, 19]. At present, stretching is the widely used treatment for shoulder dysfunction after BC [16, 17]. Continuous stretching prevents contracture, tension, and adhesion of the pectoral muscles [20]. Furthermore, stretching involves the execution of movement patterns throughout the available ROM, which can improve joint mobility, enhance muscle strength, and provide a good foundation for further exercise to achieve good results [21, 22].

However, the optimal timeline for initiating postoperative rehabilitation for BC patients is not yet clear. There are many related clinical studies, and the timing in these studies ranged from postoperative 1 day to 1 year [16]. Currently, it is commonly thought that early institution of flexion and abduction exercises following axillary dissection appears to have a harmful effect on PDV and wound healing. Adequate functional ROM is attained in all patients with minimal complications when active motion exercises are delayed for up to 7 days after axillary dissection [23]. A meta-analysis has shown that researchers are more inclined to start rehabilitation exercises early. Early and delayed exercises have not been found to cause significant differences in the incidences of delayed wound healing, wound aspiration, pain, or lymphedema [16]. Therefore, we speculate that early rehabilitation is feasible for postoperative patients. We aim to investigate the effect of different timelines of multifactorial physical therapy in postoperative BC patients.

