### Aim of this study

The aims of this study are as follows:
Observation of the optimal active exercises of the shoulder joint under full evaluation at 3 days after surgery, with respect to whether it accelerates the recovery of shoulder function and improves the quality of life of postoperative patients with BC. Evaluation of whether early-stage rehabilitation training leads to an increase in PDV, which affects shoulder function and the time of extubation in BC patients.Observation of progressive resistance training (PRT) in the case of full evaluation at 3 weeks after surgery, with respect to whether it promotes the recovery of shoulder function.

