### Training timelines

The patients will be divided into four groups: A, B, C, and D. All patients will start the rehabilitation training of phases 1 and 3 separately on the first day and the second week after surgery. The training timings of phases 2 and 4 are slightly different in different groups. Group A will start phase 2 at 1 week after surgery and phase 4 at the fourth week after surgery. Group B will also start phase 2 at 1 week after surgery, but they will start phase 4 in the third week after surgery. Group C will advance the start of phase 2 to the third day after surgery, but they will not start phase 4 until the fourth week after surgery. Group D will not only advance the start of phase 2 to the third day after surgery, but they will also initiate phase 4 to the third week after surgery, 1 week ahead of schedule.

During the trial, patients will stay in the hospital or return to the hospital regularly for chemotherapy, to ensure that they can be directly instructed. After patients are fully discharged, the training meeting will be instructed and completed in the form of a home exercise, program lasting for 6 weeks, 3–5 sets per week. A video of each patient’s exercise session should be sent to the therapist for examination.

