## Discussion

Functional axillary dissection has been widely performed in breast surgery at the Department of Thyroid and Breast Surgery of the Zhongnan Hospital of Wuhan University [40]. Surgery for BC has improved and has also been supplemented with endocrine therapy, targeted therapy, and radiation therapy to maintain high disease-free survival while reducing surgical trauma. Based on the previous research results [12, 17], this study aimed to design a more effective exercise program for postoperative patients undergoing rehabilitation. Although relevant guidelines already exist, they have not been updated regularly. Some researchers have conducted a prospective study on the timing of rehabilitation exercise, and they found that early rehabilitation exercise had no significant effect on wound healing and did not increase the risk of lymphedema [16]. We wondered whether the optimal intervention times of the rehabilitation methods recommended in the guidelines could be advanced as surgical trauma is reduced. Therefore, we set up different rehabilitation timelines combined with exercise to verify the feasibility of the earlier rehabilitation exercise process.

In the Clinical Practice Guidelines for Breast Cancer Rehabilitation, it is recommended that postoperative physical therapy should begin the first day following surgery, gentle ROM exercise should be initiated in the first week after surgery, and the resistive exercises can be started with light weights within 4–6 weeks after surgery. Active stretching exercises can be initiated 1 week after surgery, or when the drain has been removed, and they should be continued for 6 to 8 weeks or until full ROM is achieved in the affected upper extremity [18]. According to the guidelines, we designed a timeline initiating active shoulder exercises 1 week after surgery and PRT 4 weeks after surgery as the control condition for this study.

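### Aim 2 (does early training raise drainage volume) is tested across four groups, although at every drainage visit only two schedules exist; a single early-versus-late contrast with its confidence interval would answer it better

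*Protocol article*

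**What the plan says.** The second aim in the protocol article (Aim of this study) is "Evaluation of whether early-stage rehabilitation training leads to an increase in PDV". The Discussion says the different timelines were set up "to verify the feasibility of the earlier rehabilitation exercise process".

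The Statistical analyses section lists PDV with CMS, quality of life and the other outcomes under one rule: "one-way analysis of variance (ANOVA) will be performed for comparison among the 4 groups", followed by "If there is an overall difference, the Tukey method for multiple comparisons will be used to compare the differences between groups at each time point". It adds "A two-sided significance level of 5% will be used for all analyses". The fallback reads "For data with irregular variance, variable transformation can be used after the Kruskal-Wallis" test. Repeated-measures ANOVA is used to describe recovery over time. No early-versus-late contrast is given for PDV.

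Under Training timelines, "Group C will advance the start of phase 2 to the third day after surgery", and D does the same; A and B start phase 2 at 1 week. Phase 4 starts in the third week (B, D) or the fourth week (A, C). Under Secondary parameters, PDV is assessed at day 1, day 3, week 1 and week 2. The Sample size section concerns CMS only.

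**The concern.** Aim 2 is a harm question about one factor, the start of phase 2. The four groups come from crossing two factors, the start of phase 2 and the start of phase 4. The second factor has not yet acted when PDV is measured, so the four-group rule treats two pairs of identically scheduled groups as four regimens. This weakens the comparison on which the aim depends.

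The analysis also yields only significance tests. If the result is non-significant, the planned output says little about how large a rise the data still allow. At stake is whether a real rise in drainage from a day-3 start would be noticed and, if none is seen, whether the report can say how much of a rise has been excluded.

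**Working it through.** **1. Schedules at each PDV visit** (Training timelines; Secondary parameters)

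| PDV visit | A and B | C and D | Phase 4 in any group |
|---|---|---|---|
| Day 1 | phase 1 | phase 1 | no |
| Day 3 | phase 1 | phase 2 starts | no |
| Week 1 | phase 2 starts | in phase 2 since day 3 | no |
| Week 2 | in phase 2 | in phase 2 | no |

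Phase 3 starts in the second week in all groups. A and B never differ in schedule at a PDV visit, nor do C and D. Of the three between-group degrees of freedom, one is early v late; the other two are A v B and C v D. Of the six Tukey pairs, two compare identical schedules and the other four each use only half of the patients. The contrast is cleanest at week 1, because by week 2 all groups are doing phase 2.

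**2. Inputs**

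The article has no PDV power figure to reproduce. From the Sample size section I take only 50 per group and, as a pessimistic case, 50 × 0.8 = 40 per group after the 20% loss. Two-sided alpha is 0.05. Assumed, because the documents give no PDV standard deviation or relevant rise: normal data, equal SD (set to 1), and a true rise of 0.5 SD in both C and D.

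**3. Overall ANOVA**

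With means (0, 0, 0.5, 0.5), each group lies 0.25 from the grand mean. The noncentrality is λ = n × 4 × 0.25² = 0.25n, which is 12.5 (n = 50) or 10 (n = 40). The noncentral F with 3 and 4(n − 1) degrees of freedom gives miss rates of 15% and 25%.

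**4. Full rule**

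Here a detection needs a significant overall F and at least one early group significantly above a late group by Tukey. By simulation the rule misses in about 20% (n = 50) and 31–32% (n = 40) of trials.

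**5. Pooled contrast, (C+D) v (A+B)**

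Standard error = √(1/(2n) + 1/(2n)) = 1/√n, which is 0.141 or 0.158. The standardised effect is 0.5√n, which is 3.54 or 3.16. The normal approximation to the miss rate, Φ(1.96 − 0.5√n), gives 5.8% or 11.5%; the t distribution gives 6.0% or 11.8%.

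**6. Precision**

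The 95% half-width of the pooled contrast is t × 1/√n, which is 0.28 or 0.31 SD. The half-width of one Tukey pair is q/√n: 3.66/√50 = 0.52 SD or 3.67/√40 = 0.58 SD. An observed C v A difference of exactly zero would therefore not exclude a 0.5-SD rise on the Tukey interval.

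| | n = 50 per group | n = 40 per group |
|---|---|---|
| Overall ANOVA misses | 15% | 25% |
| Full rule misses | about 20% | about 31–32% |
| Pooled contrast misses | about 6% | about 12% |
| Half-width, one Tukey pair | 0.52 SD | 0.58 SD |
| Half-width, pooled contrast | 0.28 SD | 0.31 SD |

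**The case against.** A reader might infer that the trial will declare drainage unchanged whenever p exceeds 0.05. The article does not say so. Aim 2 is worded as a difference question, and a difference test is a coherent reply to it. The nearest support is the Introduction, which reports that "Early and delayed exercises have not been found to cause significant differences in the incidences of delayed wound healing, wound aspiration, pain, or lymphedema" and then speculates that early rehabilitation is feasible. That shows a habit of reading earlier studies, not a decision rule for this one.

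A reader might also quote a much larger miss rate. With C v A as the only pair that counts, the rule misses 54% at 50 per group and 64% at 40. But the article does not make C v A the test of aim 2. The 40-per-group case also applies a loss allowance from a day-84 CMS calculation to data that nurses record in the first two weeks, when loss is probably smaller. The natural case is about 50 per group with both early groups raised: 15–20% missed, or 80–85% power, which is respectable for a secondary outcome.

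Nor is a missing margin a defect here. PDV is secondary, and a margin could sit in an analysis plan that is not shown. A margin would also be demanding: with N = 200 and no true effect, the upper limit falls below 0.5 SD in 94% of trials but below 0.3 SD in only about 56% (Φ(0.3 × √50 − 1.96)).

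Finally, PDV may be skewed, so the fallback might apply and the normal-theory rates would be approximate. But Kruskal-Wallis is also a four-group difference test.

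All of this limits the size of the point. The mismatch between a four-group test and two schedules is untouched: it follows from the article's own timetable and a test that the article itself fixes.

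**Conclusion.** The point holds in a limited form. That A and B, and likewise C and D, share a schedule at every PDV visit needs no assumption. The cost of ignoring it does: for a 0.5-SD rise in both early groups with normal data, pooling cuts the miss rate from about 20% to 6% at 50 per group (from about 31–32% to 12% at 40) and nearly halves the interval width compared with a single Tukey pair. Other effect sizes would change these rates. The ratio of interval widths does not depend on the effect size.

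The documents do not support saying that the sponsor will equate non-significance with safety, or that a formal margin is required. They do support saying that the planned output could not by itself justify a claim of no increase, so the basis for any such claim should be fixed in advance.

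**What to change.** In Statistical analyses, take aim 2 out of the general rule and state:

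- The analysis of aim 2 is one pre-specified contrast of PDV between early phase 2 (C+D) and late phase 2 (A+B).
- Week 1 is the main visit, using the value from before A and B have trained in phase 2. Week 2 is supportive, because the contrast is diluted by then.
- The contrast is analysed on the log scale, as a ratio, if PDV is skewed.
- The difference or ratio is reported with its two-sided 95% confidence interval. Any statement that drainage is not increased rests on the upper limit of that interval, not on a non-significant p-value.
- ANOVA with Tukey stays for CMS and the other efficacy outcomes.

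The cost is a few sentences, with no added patients, visits or measurements. The downside is that a claim of no increase becomes harder to make. A formal margin is optional; if wanted, the sponsor's clinicians should set it before unblinding.
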